### 2.4. Sample Size Calculation

Sample size was estimated a priori using G*Power 3.1 [37]. Maximal voluntary contraction pressure (mmHg), assessed by manometric perineometry, was selected as the single primary outcome because it provides an objective and quantitative measure of PFM strength and is the outcome most directly related to the primary study hypothesis.

Previous randomized controlled trials involving women with UI have shown that vaginal manometric measures of PFM strength and endurance are responsive to exercise-based interventions incorporating specific or voluntary PFM contractions. In particular, Gonzaga et al. [38] reported improvements in manometric measures of PFM strength and endurance following PFM training and Pilates exercise performed with voluntary PFM contraction in postmenopausal women with UI. However, because previous studies are characterized by relatively small sample sizes and heterogeneous interventions and do not provide either a directly applicable standardized effect size or an established clinically important difference for the planned group-by-time comparison, Cohen’s f = 0.24 was selected as a conservative a priori planning assumption rather than an empirically derived effect estimate [39,40].

The calculation was based on a repeated-measures ANOVA model (within-between interaction; four groups; three time points: T0, T1, T2; two-tailed α = 0.05; statistical power = 1 − β = 0.80; assumed correlation among repeated measures r = 0.50; and Cohen’s f = 0.24). Under these assumptions, the minimum analytical sample required was estimated at 96 participants. Nevertheless, the planned recruitment target was set at 120 participants (30 per group). This target exceeds the minimum sample size required by the formal power calculation and was selected to preserve balanced allocation across the four intervention groups, accommodate anticipated attrition and incomplete follow-up data, and improve the precision and stability of the estimated longitudinal treatment effects obtained from the planned linear mixed-effects models (LMM). The anticipated attrition rate was conservatively estimated at 20%, based on participant retention reported in comparable randomized exercise-based interventions involving older women with UI [7,41,42].

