The primary analysis will use linear mixed-effects models (LMM) treating all three assessment time points (T0, T1, T2) as repeated observations of the outcome variable, following a constrained longitudinal data analysis (cLDA) framework. In accordance with the cLDA approach, baseline means are constrained to be equal across randomized groups, reflecting the randomization assumption while modelling T0 as the first repeated outcome. The model will include the following fixed effects: group (four levels: Control, EX, EXVERB, EXVERBPSY), time (three levels: T0, T1, T2), and their interaction (group × time). Participant will be included as a random effect (random intercept). The primary inferential interest is placed on the group × time interaction, evaluated at T1 (post-intervention, Week 18) and T2 (follow-up, Week 44). The cLDA model is robust to missing data under the missing-at-random (MAR) assumption and does not require sphericity. As a pre-specified sensitivity analysis, an ANCOVA model including baseline values as covariates will also be performed for T1 and T2 to evaluate the robustness of the primary cLDA findings [81]. The within-participant covariance of repeated measurements will be modelled using an unstructured covariance matrix. Model assumptions will be verified through inspection of residual plots, Q-Q plots, and formal tests of normality (Shapiro–Wilk) and homoscedasticity (Levene) applied to model residuals. If distributional assumptions are substantially violated, non-parametric alternatives (Friedman test for within-group comparisons; Mann–Whitney U test for between-group comparisons at each time point) will be used as sensitivity analyses, with results from both approaches reported.

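### The fixed effects listed for the primary model give each arm its own baseline mean, contradicting the stated cLDA constraint, and the random intercept is redundant beside an unstructured covariance

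*Protocol article*

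**What the plan says.** All of this stands in one paragraph of section 2.8.1 (Data Analysis Plan) of the protocol article.

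- **Constraint.** The model follows a cLDA framework in which "baseline means are constrained to be equal across randomized groups", with "modelling T0 as the first repeated outcome".
- **Mean model.** The next sentence reads "The model will include the following fixed effects: group (four levels: Control, EX, EXVERB, EXVERBPSY), time (three levels: T0, T1, T2"). To these two factors it adds a third term, the full product of group and time.
- **Random effect.** "Participant will be included as a random effect (random intercept").
- **Covariance.** "The within-participant covariance of repeated measurements will be modelled using an unstructured covariance matrix".
- **Target.** "The primary inferential interest is placed on the group × time interaction, evaluated at T1" and at T2.

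The paragraph does not say that the group term is dropped or set to zero at T0, or that the random intercept and the unstructured matrix are alternatives. Later in 2.8.1, five pairwise contrasts at T1 follow if the interaction is significant, and the H2 trend weights are applied to the group factor of the mixed model.

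**The concern.** A cLDA obtains its precision by leaving out any group difference at T0. A group main effect together with a full group-by-time interaction puts that difference back. The stated constraint and the listed terms therefore describe two different models for the single primary endpoint, and two analysts following the same paragraph could report different estimates and p-values.

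Three things are at stake:

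- the precision of the T1 and T2 contrasts;
- the power of the interaction test that opens the way to the five contrasts;
- the meaning of an arm-versus-control contrast at T1. Under cLDA the T1 mean difference and the T1 interaction contrast are one quantity. Under the listed terms they are two.

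The covariance has a smaller problem. An unstructured matrix for three visits already describes every variance and covariance, so a random intercept adds a parameter that the data cannot determine.

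**Working it through.** **Inputs.** Four groups, three time points and r = 0.50 come from the sample size calculation in 2.4 ("four groups; three time points: T0, T1, T2; two-tailed α = 0.05; statistical power = 1 − β = 0.80"), as do the 30 women per arm. Compound symmetry is the planning assumption named in the Limitations, item (vii). Unit SD, complete data and a known covariance are my assumptions. The plan gives no figure for the precision of the primary contrast, so there is none to reproduce. The minimum sample of 96 in 2.4 plays no part here.

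**1. Mean parameters**

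- Listed terms: intercept 1 + group 3 + time 2 + interaction 6 = 12 parameters for 4 × 3 = 12 cells. The rank is 12, with four free T0 means.
- cLDA: intercept 1 + time 2 + group indicators at T1 and T2 only, 3 × 2 = 6, giving 9 parameters and one T0 mean.
- Deleting only the group main effect is not enough. If the interaction still spans T0, the rank is again 12.

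One simulated trial (30 per arm, unit variances, r = 0.5) shows the difference. The listed model returned T0 means of −0.021, 0.016, 0.104 and −0.014, exactly the observed arm means. The constrained model returned 0.021 for all four arms.

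**2. Variance of one arm-versus-control contrast at T1, n = 30 per arm**

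- cLDA: 2(1 − r²)/n
- Interaction contrast under the listed terms (difference in change): 4(1 − r)/n
- Simple T1 difference under the listed terms: 2/n
- Ratio of the second to the first: 4(1 − r) / [2(1 − r²)] = 2/(1 + r)

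| r | cLDA | Interaction, listed terms | Ratio | Simple T1 difference, listed terms |
|---|---|---|---|---|
| 0.3 (assumed) | 0.0607 | 0.0933 | 1.54 | 0.0667 |
| 0.5 (protocol) | 0.0500 | 0.0667 | 1.33 | 0.0667 |
| 0.7 (assumed) | 0.0340 | 0.0400 | 1.18 | 0.0667 |

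At r = 0.50 the standard error rises from √0.0500 = 0.224 to √0.0667 = 0.258 SD, about 15%. In precision, 120 women count as 120/1.333 = 90. The two T1 quantities under the listed terms happen to have equal variance at r = 0.50, but they remain different estimates: one subtracts the observed T0 difference and the other does not.

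**3. The interaction test.** Take an equal effect at T1 and T2 with r = 0.50. Given T0, the two follow-up values have variance 1 − r² = 0.75 and covariance r − r² = 0.25, so the quadratic form is 2/(0.75 + 0.25) = 2.00. The two changes from T0 have variance 2(1 − r) = 1 and covariance 1 − r = 0.5, so it is 2/(1 + 0.5) = 1.33. The noncentrality of the test falls by one third.

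**4. Covariance parameters.** An unstructured 3 × 3 matrix has 6 parameters. Adding a random-intercept variance makes 7, mapping to 6 variances and covariances (rank 6). In the same simulated trial, fixing the intercept variance at 0, 0.1, 0.2, 0.3 or 0.4 gave the same −2 log-likelihood each time (189.14356, omitting a constant) and the same marginal covariance matrix. Only the split between the two components is undetermined.

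**The case against.** The strongest defence is that the constraint is written out in plain words directly before the list. The list can be read as naming the model's factors, and exact coding is usually left to an analysis plan. A careful analyst could fit the right model. That much stands: the list is inconsistent with the constraint but does not override it. It does not remove the point, because the article chose to state the terms and, as stated, they specify a different model. The trend analysis also refers to a group factor in the model, which invites the literal reading.

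A reader might infer more than the text supports, in four respects.

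- **That treatment effects would be biased.** They would not. Under randomization the unconstrained interaction contrast is unbiased, and the loss is one of precision.
- **That baseline data are discarded.** The named target is the interaction, which uses T0 inefficiently as a change score. Only a simple T1 difference ignores T0. Its variance at r = 0.7 is 1.96 times that of cLDA (0.0667/0.0340), but the plan does not name it as the target, so that figure is not the size of the problem.
- **That the software must fail.** Convergence or Hessian warnings are possible, but failure was not shown in SPSS or R mixed-model procedures. An arbitrary split with sound treatment estimates is another possible outcome.
- **That a failed fit would force a data-dependent choice of covariance.** Dropping the redundant intercept leaves exactly the unstructured matrix that 2.8.1 already specifies.

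The baseline-adjusted ANCOVA planned as a sensitivity analysis would supply an efficient estimate alongside. That softens the loss, but it leaves the primary analysis, as listed, less precise than the check on it.

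**Conclusion.** The point holds as an internal contradiction in the primary model. The listed fixed effects are those of the unconstrained model, and the paragraph claims the constrained one.

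If the list is fitted literally, the variance of the T1 interaction contrast is 33% larger at the protocol's r = 0.50, and between 18% and 54% larger over an assumed r of 0.7 down to 0.3. The T1 mean difference also separates from the interaction contrast. These sizes rest on compound symmetry, complete data, 30 per arm and a known covariance. The protocol expects 20% attrition, so the absolute variances would be larger in practice. If the analyst follows the sentence on the constraint instead, there is no loss.

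The random intercept is redundant. Its variance is not identified, but treatment estimates and the marginal covariance do not depend on it.

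**What to change.** Replace the sentences on fixed effects, random effect and covariance with wording such as: *Fixed effects: time (T0, T1, T2) and group-by-time indicators at T1 and T2 only, with no group term at T0; unstructured residual covariance within participant, no random intercept.*

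Code the six post-baseline group indicators explicitly in SPSS or R, since a standard interaction term restores the T0 cells.

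Say that the five pairwise contrasts and the H2 trend are linear combinations of these indicators. With control as reference, the T1 trend is −1 × EX + 1 × EXVERB + 3 × EXVERBPSY, and the control weight of −3 multiplies zero.

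The cost is a few lines of text. No data, visits or sample size change. It should be settled before the blinded analysts fit the model.

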**H3.** 
*Improvements observed immediately post-intervention will be partially maintained at 6-month follow-up, with greater long-term retention observed in the EXVERBPSY group.*

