For the planned comparisons and multiplicity controls, when a significant group × time interaction is found for the primary endpoint (α = 0.05, unadjusted), the following five pre-specified pairwise contrasts will be conducted simultaneously within a single testing family, with sequential Holm–Bonferroni correction applied across all five contrasts at each time point [82]: EXVERBPSY vs. Control at T1; EXVERB vs. Control at T1; EX vs. Control at T1; EXVERBPSY vs. EXVERB at T1 and EXVERB vs. EX at T1. Contrasts 1–3 evaluate the superiority of each active intervention arm over the educational control, directly addressing H1. Contrasts 4–5 evaluate the incremental contribution of each sequentially added component—PSY support and PFM activation instructions, respectively—consistent with the additive design of the trial. The same family of five contrasts will be repeated at T2 to evaluate the persistence of effects at the 6-month follow-up, addressing H3. Between-group effect sizes will be reported as Cohen’s d with 95% confidence intervals for each planned pairwise contrast, and as partial eta-squared (η^2^p) with 95% confidence intervals for the overall group × time interaction F-test. The same family of planned pairwise comparisons will also be applied to secondary outcomes. For each outcome analysed, sequential Holm–Bonferroni correction will be applied across the five pre-specified pairwise contrasts at each time point to control the family-wise error rate within that outcome [82].

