To formally evaluate the dose–response pattern hypothesized in H2, a pre-specified linear trend analysis will be conducted using orthogonal polynomial contrasts applied to the group factor within the LMM framework. The four groups will be assigned contrast weights reflecting the sequential addition of intervention components and their expected incremental dose: Control = −3, EX = −1, EXVERB = +1, EXVERBPSY = +3. These weights correspond to the standard orthogonal polynomial contrast coefficients for four equally spaced ordered groups [40]. This analysis therefore assumes equally spaced incremental treatment effects across the four study arms and is intended to test the prespecified hypothesis of a monotonic additive dose–response trend, rather than implying that the additional intervention components are biologically or clinically equivalent. A statistically significant positive linear contrast at T1 will be interpreted as confirmatory evidence supporting a monotonic dose–response relationship across the additive intervention arms, consistent with H2. Results at T2 will be interpreted as exploratory, addressing the persistence of the dose–response pattern at follow-up. The effect size for the linear trend will be reported as r^2^contrast = Fcontrast/(Fcontrast + dferror). This analysis will be conducted for the primary endpoint and, as exploratory analyses, for the pre-specified secondary outcomes.

All secondary and exploratory outcomes will be analysed using the same LMM framework. Sequential Holm–Bonferroni correction will be applied across the five pre-specified pairwise contrasts for each secondary outcome, consistent with the primary analysis. However, no global family-wise error rate correction will be applied across secondary outcomes. Results will be presented with adjusted *p*-values for the planes pairwise comparisons, Cohen’s d effect sizes with 95% confidence intervals, and η^2^p for global F-tests. Findings from the prespecified secondary outcomes will be interpreted as supportive rather than confirmatory, whereas exploratory outcomes will be interpreted as hypothesis-generating.

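### The five T1 contrasts on the primary endpoint must wait for a significant group × time interaction, although Holm already protects them; for that family the condition only costs power

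*Protocol article*

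**What the plan says.** All of this is in Section 2.8.1 of the protocol article, unless noted.

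- The model has fixed effects "group (four levels: Control, EX, EXVERB, EXVERBPSY), time (three levels: T0, T1, T2), and their interaction (group × time"), and "baseline means are constrained to be equal across randomized groups".
- "The primary inferential interest is placed on the group × time interaction, evaluated at T1"; the sentence goes on to name T2 as well.
- The contrasts on the primary endpoint are conditional: "when a significant group × time interaction is found for the primary endpoint (α = 0.05, unadjusted), the following five pre-specified pairwise contrasts" follow. They are EXVERBPSY, EXVERB and EX each against Control, EXVERBPSY against EXVERB, and EXVERB against EX.
- They are tested "with sequential Holm–Bonferroni correction applied across all five contrasts at each time point".
- "The same family of five contrasts will be repeated at T2 to evaluate the persistence of effects at the 6-month follow-up". This is a second Holm family at 5%.
- The effect-size sentence refers to a single overall interaction F-test.
- The linear trend over the four arms at T1 is called confirmatory, and no interaction condition is stated for it.
- H3, in the Introduction: "Improvements observed immediately post-intervention will be partially maintained at 6-month follow-up", with better retention expected under EXVERBPSY.

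**The concern.** Two protections are stacked on one family. Holm controls the family-wise error of the five T1 contrasts whatever the true effects are, so the interaction test in front of it adds no needed protection there. It can only remove rejections.

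The interaction test also looks at more than T1. With baseline means constrained equal, it asks whether the groups differ at T1 or at T2. If effects shrink by T2, three of its six degrees of freedom carry little signal, and the test can miss a T1 difference that Holm would have declared. H3 anticipates this pattern.

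At stake are the pairwise comparisons that Section 2.8.1 ties to H1 and to the added value of each component. A T1 contrast that would pass Holm could go formally untested.

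**Working it through.** **Plan's own figures.** The plan gives no power or error rate for the conditional procedure, so there is none to reproduce. Inputs from Section 2.4 are α = 0.05 two-sided, correlation r = 0.50, f = 0.24, analytical sample 96 (96/4 = 24 per arm) and recruitment 120 (30 per arm).

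**Degrees of freedom (inferred, not printed).** (4 − 1)(3 − 1) = 6. With equal baseline means these are 3 group differences at T1 plus 3 at T2.

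**Holm on five contrasts.** Ordered p-values are compared with 0.05/5 = 0.010, 0.05/4 = 0.0125, 0.05/3, 0.05/2 and 0.05.

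**Simulation.** Normal data, SD 1, r = 0.5 between all time points, complete data, at least 20,000 trials per scenario. Contrasts are baseline-adjusted t-tests. The interaction test is the exact 6-df Wilks test of group on (T1, T2) adjusted for T0, the complete-data counterpart of the constrained model. Independent runs agree to within about 1–2 points. Effects in SD units and the retention at T2 are assumptions; the documents give neither.

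Chance of at least one Holm-significant T1 contrast:

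| T1 effects: Control/EX/EXVERB/EXVERBPSY | Kept at T2 | Per arm | Holm alone | With condition | Loss (points) |
|---|---|---|---|---|---|
| 0/0.2/0.5/0.8 | half | 24 | 75% | 65% | 10 |
| | half | 30 | 86% | 79% | 7 |
| | EXVERBPSY 75%, others half | 24 | 75% | 69% | 6 |
| | EXVERBPSY 75%, others half | 30 | 86% | 82% | 4 |
| | all | 24 | 75% | 73% | 2 |
| | all | 30 | 86% | 85% | 1 |
| 0/0.6/0.6/0.6 | half | 24 | 65% | 51% | 14 |
| | half | 30 | 77% | 64% | 13 |
| | all | 24 | 66% | 60% | 6 |
| | all | 30 | 77% | 73% | 4 |
| 0/0.25/0.5/0.75 | none | 24 | 69% | 60% | 9 |
| | half | 24 | 69% | 57% | 12 |
| | all | 24 | 69% | 65% | 4 |
| | half | 30 | 80% | 71% | 9 |
| 0/0/0.75/0.75 | half | 24 | 89% | 86% | 3 |
| | half | 30 | 95% | 94% | 1 |

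For EXVERBPSY against Control alone (first pattern, half kept, 24 per arm) the figures are 71% and 63%.

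**What f = 0.24 implies.** For equal steps with top effect D at T1 and a fraction kept at T2, the SD of the interaction effects over the 12 cells is √(variance of the arm scores × mean square of the centred time profile).
- Variance of (0, 1/3, 2/3, 1) = 0.1389.
- T2 effect gone, or fully kept: profile mean square 2/9, so the SD is √(0.1389 × 2/9) = 0.176 per unit of D.
- Half kept: mean square 1/6, so the SD is 0.152.
- If f is that SD in raw units, D = 0.24/0.176 = 1.37 or 0.24/0.152 = 1.58, and the condition costs at most 0.1 point.
- If f is scaled by √(2 × 0.5/3) = 0.577 (Cohen's convention), D = 0.79 or 0.91. With fading, the loss is then 8–9 points at 24 per arm and 4.5–6 at 30.

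**Error rates.**

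| Situation | Family | Holm alone | With condition |
|---|---|---|---|
| No effect anywhere (24 per arm) | T1 | 4.2% | 2.0% |
| No effect anywhere (24 per arm) | T1 and T2 | 8.1% | 3.7% |
| Some large true effects (three scenarios) | T1 | 3.9–4.8% | the same |
| Some large true effects (three scenarios) | T1 and T2 | 7.8–8.6% | the same |

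**Alternative reading of the condition.** If it means a T1-only test with 3 df, the first pattern with half kept gives 74.5% against 73.4% at 24 per arm and 85.9% against 85.4% at 30. The second pattern gives 65.2% against 63.2% at 24.

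**The case against.** The strongest case for the plan is that the trial was sized on the interaction and makes that interaction its main inference. An omnibus test followed by protected contrasts is conventional and valid, merely conservative. That stands: nothing here is an error-rate fault.

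Several stronger readings are tempting, and the documents do not support them.

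- *The condition buys no error control at all.* This is true only within T1. The plan has two Holm families, and the condition roughly halves the global-null error over both. That is weak control and vanishes once a real effect satisfies the condition, but it is a gain.
- *A 6-df test is specified.* It is inferred. The word overall appears in the effect-size sentence, not in the conditional one, and the sentence on primary inference names T1 and T2 separately. A 3-df T1 condition is possible and would cost 0–2 points.
- *A fading T1 effect disappears from the trial.* The confirmatory T1 trend has no stated condition, separate ANCOVAs at T1 and T2 are planned as sensitivity analyses, and effect sizes with intervals are promised for each contrast. Only the formal pairwise tests are affected.
- *Secondary outcomes are tested more leniently than the primary.* For them the text says "Sequential Holm–Bonferroni correction will be applied across the five pre-specified pairwise contrasts for each secondary outcome" and repeats no interaction condition, but it adds that this is consistent with the primary analysis. The intent is unclear, and those findings are only supportive.

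The size of the loss also rests on chosen scenarios. Half retention in every arm is unfavourable and leaves out the better retention that H3 expects under EXVERBPSY. Allowing for that cuts the loss from 10 to 6 points at 24 per arm and from 7 to 4 at 30.

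**Conclusion.** The point holds for the five pairwise T1 contrasts on the primary endpoint. Holm alone keeps that family within 5%, so the interaction condition lowers power there without being needed.

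On the 6-df reading, with assumed effects of about 0.6–0.8 SD that are graded or equal over the exercise arms and partly fade, the loss is about 6–14 points at 24 per arm and 4–13 at 30. With full persistence it is about 1–3 points in the graded pattern and up to about 6 in the others. It shrinks to 1–3 points where power is already near 90% or more (0.75 SD in the two PFM arms), and to almost nothing for very large effects or a T1-only condition.

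These figures assume complete data and equal correlations of 0.5. This is an avoidable loss of power that a wording change removes, not a threat to validity.

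**What to change.** In Section 2.8.1:

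1. Remove the interaction condition. Test the five T1 contrasts on the primary endpoint directly from the mixed model, with Holm at two-sided 5%, and name them the confirmatory pairwise family.
2. Report the overall interaction F-test alongside as a global result.
3. Keep Holm within T2, but label the T2 contrasts as supportive evidence of persistence, not a second confirmatory family.

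Two alternatives should be avoided. A single ten-contrast Holm over T1 and T2 starts at 0.05/10 = 0.005 and gives back most of the gain: in the first pattern, half kept, 24 per arm, T1 success is 66%, against 65% with the present condition and 75% with Holm over the five T1 contrasts. Testing a T2 contrast only where the same T1 contrast was rejected, with each family at 5%, does not strongly control error over both times.

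Cost: no patients and no data. Under the global null the T1 family-wise error rises from about 2% to about 4%, still within 5%, and T2 pairwise results are no longer confirmatory. The change alters the statistical analysis, so under Section 3.2 it goes to the Ethics Committee before implementation and, where applicable, to the registry. It should be made before any unblinded analysis.
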